## Abstract

**Introduction:**

Cardiovascular diseases (CVD) are the leading cause of death globally, taking an estimated 17. 9 million lives each year. Cardiac rehabilitation is shown to reduce mortality and hospital readmissions, while improving physical fitness and quality of life. Despite the recommendations and proven benefits, acceptance and adherence remain low. Mobile health (mHealth) solutions may contribute to more personalized and tailored patient recommendations according to their specific needs. This study protocol aims to assess the effectiveness of a user-friendly, comprehensive Clinical Decision Support System (CDSS) for remote patient monitoring of CVD patients, primarily on the reduction of recurrent cardiovascular events.

**Methods and Analysis:**

The study will follow a multicenter randomized controlled design involving two cardiology units in the Center Region of Portugal. Prospective CVD patients will be approached by the healthcare staff at each unit and checked for eligibility according to the predefined inclusion/exclusion criteria. The CDSS will suggest a monitoring plan for the patient, will advise the mHealth tools (apps and wearables) adapted to patient needs, and will collect data. The clinical study will start in January 2023.

**Discussion:**

The success of the mHeart.4U intervention will be a step toward the use of technological interfaces as an integrating part of CR programs.

**Ethics and Dissemination:**

The study will undergo ethical revision by the Ethics Board of the two hospital units where the study will unfold. The study was registered in ClinicalTrials.gov on 18th January 2022 with the number NCT05196802. The study findings will be published in international peer-reviewed scientific journals and encounters and in a user-friendly manner to the society.

## Introduction

Cardiovascular diseases (CVD) are the most common non-communicable diseases globally, accounting for an estimated 17.9 million deaths per year (1). They are the leading cause of mortality worldwide, with the number of deaths increasing by 14.5% between 2006 and 2016 (2). The reduction of CVD-related mortality and morbidity is a key global health priority for the World Health Organization (WHO) (3) and the United Nations (UN) Sustainable Development Goals (4).

The American Heart Association and the European Society of Cardiology suggest that cardiac rehabilitation (CR) is a Class IA recommendation for patients with CVD. Substantial benefits include reducing mortality by 20 to 47%, reducing hospital readmissions by 18%, improving physical activity, reducing cardiovascular risk factors and improving quality of life (5, 6). Despite the proven benefits, low rates of adherence (14 to 35.5%) in traditional CR programs continue to limit treatment impact, due to inadequate access, time conflicts and associated costs (5, 7).

Rapid advances in mobile wireless communications and wearable sensor technologies may bridge the gap between home- and center-based delivery models by combining availability, accessibility, and responsive individualized clinical oversight (8). These technologies have the potential to overcome some of these barriers and may be a valuable instrument for promoting adherence. Mobile technologies are recognized for benefits such as bridging time and distance barriers to clinical oversight and increasing accessibility to care that is traditionally delivered face-to-face (9).

Particularly in relation to CR, studies reveal that technology-mediated interventions are equally effective in improving health outcomes compared to conventional care, dissipating fears referred by both clinicians and patients in relation to achieving similar results with virtual methods (10, 11). Studies specifically evaluating the effectiveness of mHealth-mediated CR interventions have revealed positive impact on composite and combined scores involving cardiovascular morbidity (e.g., worsening heart failure), hospitalizations or readmissions due to cardiovascular causes (e.g., unplanned revascularization) and cardiovascular mortality (12).

The COVID-19 era has been of enormous importance for the clinical implementation of digital health and wearable devices (13). Due to this pandemic, outpatient visits of chronic patients have been replaced by virtual visits to limit disease transmission. Health-related mobile apps (mHealth) have many advantages such as enabling continuous monitoring of patient health status, receiving health-related knowledge and automated feedback, and improving quality of life (14–17). Studies have shown that the use of mHealth interventions increases motivation and participation in CR programs (8, 18). In 2017, there were an estimated 3.7 billion mHealth app downloads (19), highlighting their practicality and convenience.

However, there is still a lack of qualitative data about which mobile app features are more engaging over time, thus contributing to behavior change and increasing treatment adherence (1). The heterogeneity of features in these apps leads to the need of identifying which of them can better contribute to disease self-management (20).

Wearables may also provide a benefit through increased health awareness, democratization of health data and patient engagement (13). The widespread use of heart rate and fitness tracking technologies provides unparalleled opportunities for capturing physiological information. While the number of patients meeting healthcare providers with wearables is rapidly growing, the European Society of Cardiology (13) highlights that there are few clinical guidelines on how to use these data and that technical aspects of heart rate tracking need to be further validated. The use of continuous monitoring may allow early risk detection, thereby becoming novel applications in both prevention and clinical research (13). A recent systematic review (5) evaluated the effects of eHealth CR on health outcomes, showing a significant promotion of physical activity, daily steps, quality of life (QoL) and a reduction in rehospitalization.

Time constraints, patient overpopulation, and complex guidelines require alternative solutions for real-time patient monitoring. Rapidly evolving e-health technology combined with clinical decision support systems (CDSS) provides an effective solution to these problems (21). There are several computerized CDSS for chronic diseases management, however, to the best of our knowledge, there are none for the management of CVD patients.

Scoping the literature on remote monitoring of cardiovascular patients through mHealth tools, a few clinical study protocols can be found in recent years, aiming at determining the effect of these resources on both clinical (e.g., cardiovascular events) and process outcomes (e.g., hospital readmissions) (22, 23). Although overlapping the effect aimed through the mHeart.4U, the current study protocol adds to the previous as it builds on existing mHeath tools for monitoring and rehabilitation of cardiovascular patients with the integration of AI for personalized selection of the rehabilitation plan. Accordingly, the mHeart.4U trial will aim to reinforce the evidence on outcomes that inform clinical decision-making, such as rehospitalizations and health-related QoL, while following a sustainable approach to intervention research, wherein existing evidence and resources are pragmatically adapted and adopted to fit the real-world practice (24).

The current study protocol will innovatively explore CDSS for management of CVD patients building on existing mHealth-based interventions for cardiac monitoring and rehabilitation. We hypothesize that an mHealth intervention supported by a CDSS will reduce recurrent cardiovascular events, will promote QoL, treatment adherence, adoption of a healthier lifestyle, and Body Mass Index (BMI) reduction. Therefore, the objective of the mHeart.4U clinical study will be to determine the effectiveness of an intervention using a CDSS for remote patient monitoring, selecting the best mHealth tools (apps and wearables) according to the needs of each CVD patient and managing clinical data.

## Methods and Analysis

The mHeart.4U trial is designed in accordance with the methodology adopted for mHealth-based interventions for remote monitoring and rehabilitation trials involving CVD patients (5). Accordingly, the study will follow a pragmatic, multicenter, two parallel arms (1:1), prospective, randomized controlled design with blinded endpoint assessment, involving two cardiology units in the Center Region of Portugal. This study is a pragmatic trial because it examines the outcomes of the experimental intervention compared with a standard intervention under circumstances which closely approximate the real world (25). Additionally, personnel undertaking outcome assessment will be blinded to group allocation. The Standard Protocol Items: Recommendations for Interventional Trials reporting guidelines were used to write this protocol (26).

### Participants

Eligible participants will be adults (18+ years old) attending these cardiology outpatient clinics after the onset of an acute cardiac event, or those engaged in a structured CR program. Inclusion criteria also consider the need to be able to communicate with the researcher. Participants will be excluded if they have New York Heart Association class III/IV heart failure, terminal disease, or significant non-CVD exercise limitations.

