### Procedures

Sample recruitment will have the support of the clinical staff of the outpatient clinics based on inclusion and exclusion criteria. All eligible participants will be asked to fill out the informed consent. Participants will be randomized at a 1:1 ratio to receive usual care composed by CR alone (control group) or the mHeart.4U program (intervention group). Treatment allocation will follow a computer-generated schedule prepared by a biostatistician. The randomization schedule will be stratified by gender and trial center and will use random permuted blocks (Figure 1). The control group will follow the standard treatment protocol (27), while the Intervention group will, additionally, participate in the mHEART.4U intervention (Figure 1).

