### Statistical Analysis

The patient characteristics in the two arms at baseline will be compared descriptively using chi-squared tests for the binary and categorical variables and an unpaired Student's *t*-test for the continuous variables. One-sample *t*-test will be performed to measure the differences within the same group.

The primary outcome will be analyzed using a generalized linear mixed model, adjusting for the stratification variables (i.e., gender, hospital unit). Logistic regression will be conducted in order to explore predictive relationships of the baseline categorical variables (e.g., age, clinical variables) on the primary outcomes in both groups.

Analyses to determine the study primary outcome will be performed on the principle of intention-to-treat. Accordingly, assuming there will be a reasonable amount (>5%) of missing data, analyses to determine the primary outcome will be conducted using a multiple imputation model. A per-protocol analysis will be conducted with complete cases to test the robustness of intervention effects under different assumptions. Subgroup analyses will be conducted to determine intervention effects by gender and trial center. All statistical tests will be 2-sided at α = 0.05. The biostatistician will remain blinded throughout the analysis of treatment effects.

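### The primary model adjusts only for gender and hospital unit and forgoes the precision in age and the baseline risk score; separately, the background care of patients not in CR at entry needs one clear statement

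*Protocol article*

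**What the plan says.** **Primary model.** Under Statistical Analysis the primary outcome is analysed with a "generalized linear mixed model, adjusting for the stratification variables (i.e., gender, hospital unit". This matches the randomisation: "The randomization schedule will be stratified by gender and trial center and will use random permuted blocks". The same section plans a further logistic regression to explore whether baseline variables, with age and clinical variables as its examples, predict the primary outcome. That regression is not the primary analysis.

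**Baseline data.** Table 1 (Outcomes and Measurements) schedules age, within the sociodemographic questionnaire, and cardiovascular risk by SCORE at T0.

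**Population and comparator.** Participants admits adults attending the outpatient clinics "after the onset of an acute cardiac event, or those engaged in a structured CR program". Procedures randomises them "to receive usual care composed by CR alone (control group) or the mHeart.4U program (intervention group", and later in the same paragraph states: "The control group will follow the standard treatment protocol (27), while the Intervention group will, additionally, participate in the mHEART.4U intervention".

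**The concern.** There are two separate issues.

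1. The article itself names age and clinical variables as candidate predictors of the primary outcome and collects them before treatment starts, but leaves them out of the analysis that will decide the trial. For a binary outcome with few events, leaving out a prognostic baseline variable costs power. The loss is avoidable because the data are already in the schedule.

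2. The eligibility sentence joins two routes with an *or*, so a post-event outpatient who is not in CR qualifies. Control is then described once as CR alone and once as a standard treatment protocol. For such a patient, the article does not say whether CR is started after allocation or what usual care consists of. What is at stake is how the result is described: as mHealth added to CR, or as mHealth added to whatever each clinic provides.

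**Working it through.** **Inputs from the article (Sample Size Calculation, Statistical Analysis).** Control 13%, intervention 6%, two-sided 0.05, 80% power, 20% loss, 330 per arm.

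**Reproducing the stated size.** With the pooled two-proportion formula and mean rate 0.095:

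n = [1.96·√(2·0.095·0.905) + 0.8416·√(0.13·0.87 + 0.06·0.94)]² / 0.07² = [0.8128 + 0.3465]² / 0.0049 ≈ 274.3, so 275. Then 275 × 1.2 = 330, as stated.

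After 20% loss, 330 × 0.8 = 264 remain per arm, with power of about 78.5%. Expected events: 264 × (0.13 + 0.06) ≈ 50.

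**Gain from baseline covariates.** The article does not say how well age and SCORE predict the outcome, so their combined c-statistic is an assumption, taken from 0.64 to 0.75. Model: logit(p) = intercept + treatment + slope × standard normal score, with intercepts set so that the arm rates are 13% and 6%, and 264 per arm. Each simulated trial is analysed by logistic regression with and without the score (Wald test). Two independent simulations gave:

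| Assumed c | 6,000 runs: without → with | Gain | 8,000 runs: without → with | Gain |
|---|---|---|---|---|
| 0.64 | 79.3% → 80.2% | 0.9 | 79.1% → 80.0% | 0.9 |
| 0.71 | 79.4% → 81.8% | 2.4 | 79.3% → 81.7% | 2.4 |
| 0.75 | 78.7% → 82.5% | 3.9 | 78.4% → 82.5% | 4.0 |

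Gains are in power points, computed before rounding. The paired standard error of each gain is about 0.2 to 0.3 point.

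**Gain from CR status alone.** Take the 18% lower readmission with CR quoted in the Introduction as a risk ratio of 0.82, an assumed half of patients in CR, and a constant treatment risk ratio of 6/13.

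- Control rates: 0.13/(0.5·0.82 + 0.5) = 14.3% without CR and 11.7% with CR. Intervention rates: 6.6% and 5.4%.
- Sum of the two arms' binomial variances per patient: 0.1695 ignoring CR, 0.1693 within CR strata; ratio 0.999.
- Wald power at 264 per arm: 78.89% → 78.94%.

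Varying the share in CR from 14% to 75% keeps the gain below 0.1 point. With a stronger assumed CR risk ratio of 0.5, the largest gain is 0.6 point (78.9% → 79.5%, at a 75% share).

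**Chance imbalance in CR status.** At a 50% share the 95% range is ±1.96·√(2·0.5·0.5/330) = ±7.6 points. Multiplied by the 2.6-point difference in control rates, this moves the risk difference by about 0.2 point, against a planned 7.

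**Planned size and the CR mix.** If 13% applies to CR patients and others have 13/0.82 = 15.9%, power at 264 per arm lies between 78.5% (all in CR) and 86.8% (none in CR). The ambiguity does not undermine the sample size.

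**Effect by CR status.** With an assumed 35% in CR and the planned rates in both groups, expected events are 12.0 and 5.5 among 92.4 CR patients per arm, and 22.3 and 10.3 among 171.6 others per arm.

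- Var(log RR), CR: 1/12.0 + 1/5.5 − 2/92.4 ≈ 0.242.
- Var(log RR), others: 1/22.3 + 1/10.3 − 2/171.6 ≈ 0.130.
- Standard error of the interaction: √0.372 = 0.61. The 95% interval for the ratio of risk ratios runs a factor of exp(1.96·0.61) ≈ 3.3 either way.

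**The case against.** **On the covariates.** Adjusting for exactly the stratification factors is a coherent and valid primary analysis, gender is itself baseline information, and extra covariates are often left to an SAP that is not shown here. The assumed c-statistics have no support in the article. Most of this stands: the omission is not an error, and the size of the gain is conditional. However, the article does not leave the covariate set open. It lists it, and it sends age and clinical variables to another regression. If the full SAP already includes them in the primary model, nothing needs changing beyond aligning the text.

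**On eligibility and control.** A reader might infer that the two sections contradict each other and that part of the trial tests mHealth without CR. The article does not support that. Participants says who may enter; Procedures says what they are randomised to receive, so a patient not in CR at entry could be given CR after allocation. The standard treatment protocol carries the same reference number that the Intervention section cites among its CR guidelines. CR as background care in both arms is therefore a fair reading. The participant flowchart, which may settle it, is not available in the text reviewed. What remains is that no sentence says so.

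**On CR status as a missing factor.** A reader might also infer that omitting CR status from the strata and the model biases the result, citing the 14 to 35.5% figure in the Introduction. That figure is adherence to traditional CR programmes, not this trial's entry mix. The quoted benefits of CR make entry route prognostic only if first-route patients never receive CR, which is the open question. Randomisation balances CR status in expectation, so there is no bias.

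**Conclusion.** The point holds as an efficiency improvement plus a request for clarification.

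- The primary model is valid but leaves precision unused. The gain from age and the baseline risk score is about 1 point at c = 0.64, 2.4 at 0.71 and just under 4 at 0.75. It rests on the assumed c-statistic, the planned 13% v 6%, and 264 completers per arm.
- What the article says about entry and about control care is ambiguous for patients not in CR at entry. This affects how the comparison is described, not the validity of the estimate or the sample size.
- Leaving CR status out causes no bias and costs under 0.1 power point on the article's own CR effect, at most about 0.6 under a stronger assumption. Stratifying by it would not correct a defect, and an interaction estimate could not show whether the intervention works differently with and without CR.

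**What to change.** 1. In Statistical Analysis, prespecify age and the T0 SCORE value as continuous covariates in the primary model, alongside gender and centre. Keep the exploratory regression as exploratory. Cost: one sentence; both values are already scheduled at T0.

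2. Reconcile Participants and Procedures with a statement of the background care that both arms receive, including patients not in CR at entry, and use one description of control throughout. Which care that is remains for the investigators to state. Cost: one or two sentences.

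3. Optionally, record CR participation (yes/no) at randomisation and include it as a further covariate. The benefit is description, not power. Stratifying by it is also optional; it would double the strata from 4 to 8 for 660 patients. Label any effect by CR status as descriptive.

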### Procedures

Sample recruitment will have the support of the clinical staff of the outpatient clinics based on inclusion and exclusion criteria. All eligible participants will be asked to fill out the informed consent. Participants will be randomized at a 1:1 ratio to receive usual care composed by CR alone (control group) or the mHeart.4U program (intervention group). Treatment allocation will follow a computer-generated schedule prepared by a biostatistician. The randomization schedule will be stratified by gender and trial center and will use random permuted blocks (Figure 1). The control group will follow the standard treatment protocol (27), while the Intervention group will, additionally, participate in the mHEART.4U intervention (Figure 1).

**Figure 1 F1:**
[figure not shown]
Participant's flowchart.

### Intervention

The mHEART.4U intervention will include the use of an online CDSS for remote patient monitoring. The CDSS rule sets will be developed according to the knowledge on: (a) self-management and monitoring needs and difficulties of CVD patients and requirements of healthcare professionals, and (b) functional and technical characteristics of available mHealth tools for promoting CR.

According to the patient's needs and profile, the CDSS will suggest a monitoring plan accordingly. The mHEART.4U intervention kit will include mobile apps and wearables, such as heart rate, blood pressure, peripheral oxygen saturation (SpO2), sleep and step trackers, symptoms, lifestyle self-monitoring tools, medication reminders or motivational resources. The resources composing each intervention kit will be defined upon initial assessment of the patient's needs and in a shared decision-making process according to co-established therapeutic goals (Figure 2). Smartphones and/or wearables may be lent if necessary.

**Figure 2 F2:**
[figure not shown]
Overview of the mHeart.4U framework and functioning.

Intervention length will be 6 months and will take into account the most recent guidelines on CR (27, 28).

### Outcomes and Measurements

Outcome measurements will be carried out at the 3-month (T1) and the 6-month interventions (T2) (Table 1).

**Table 1 T1:** Schedule of assessments.

**Assessments**	**Measure**	**T0**	**T1**	**T2**
Recurrent cardiovascular event				
Cardiovascular	Patient health records		x	x
Rehospitalization	Death certificates			
Cardiovascular urgent visit				
Unplanned revascularization				
Cardiovascular mortality				
Worsening heart failure				
Quality of Life	MacNew heart disease health-related Quality of life questionnaire	x	x	x
Adherence to treatment	Therapeutic self-care scale	x	x	x
Anthropometric measures	Patient health records (BMI, waist circumference)	x	x	x
Nutrition	Health-promoting lifestyle profile-II	x	x	x
Physical activity	Health-promoting lifestyle profile-II	x	x	x
Clinical data	Patient health records	x	x	x
Blood pressure, heart rate,	Systematic coronary risk evaluation			
blood biomarkers, pathological				
history, cardiovascular risk				
Sociodemographic Data	Sociodemographic questionnaire	x		
Gender, age, academic				
qualifications, profession				
mHEART.4U usage	Utilization rate, consulted resources, self-monitoring data		x	x

*T0, Baseline assessment; T1, 3-month intervention assessment; T2, 6-month intervention assessment*.

The primary outcome will be the reduction of recurrent cardiovascular events, which is a composite of (i) cardiovascular rehospitalization or urgent visit; or (ii) unplanned revascularization; (iii) cardiovascular mortality; or (iv) worsening heart failure (29, 30).

Secondary outcomes measures will include:

a) Quality of Life, assessed through the MacNew Heart Disease Health-related Quality of Life (HRQL) questionnaire (MacNew) (31).

Acknowledging the importance of including patient's perspectives on health outcomes, the MacNew is a self-reported questionnaire that has been validated and used with both patients with experience of a myocardial infarction, and patients with experience of angina. The measurement instrument is composed of 27 items, scored from 1 (poor) to 7 (high), to assess global HRQL, physical limitations, emotional and social functions. The MacNew is currently validated to many languages including Portuguese, where it appears to be a reliable, valid and moderately responsive instrument to evaluate HRQL of people after a diagnosis of acute coronary syndrome (32);

b) Adherence to treatment, assessed through the Therapeutic Self-care Scale (TSC) (33).

The TSC includes 12 items to be answered on a 5-point Likert scale, from 0 (no) to 5 (yes) in relation to the level of knowledge during situations related to therapeutic self-care management, with higher scores corresponding to high level performance in therapeutic self-care. The measurement instrument is composed of four domains to assess patients' ability to engage in self-care activities related to: (1) taking medications as prescribed by the doctor; (2) identifying and managing symptoms; (3) performing activities of daily living; and (4) managing changes in condition. The instrument can be administered either to patients admitted to hospital with a variety of acute medical and surgical conditions, or to home-based care patients. The TSC has been widely used and is validated to various cultural contexts, including Portugal (34). The original scale has a strong internal consistency (Cronbach's α 0.93), also replicated in the Portuguese version (Cronbach's α 0.979);

c) Nutrition and Physical Activity, assessed through the Health-Promoting Lifestyle Profile-II (HPLP-II) (35).

The HPLP-II is a self-reporting instrument composed of 52 items to be answered on 4-point Likert scale (never, sometimes, often, routinely) in order to assess health-promoting behaviors as a multidimensional pattern of self-initiated actions and perceptions that serve to maintain or increase the level of wellbeing, self-fulfillment, and self-satisfaction. Nutrition (N, nine items) and Physical Activity (PA, eight items) are two of the six domains assessed, the others being: health responsibility (HR), spiritual growth (SG), interpersonal relations (IR), and stress management (SM). The original measurement instrument was tested with an α coefficient of 0.943. It has been used and validated to several languages and cultural contexts, including Portugal with psychometric results showing an adequate fit to a 52-item, six-factor structure and global Cronbach's α of 0.925 (α of N = 0.726; α of PA = 0.835) (36);

d) Anthropometric measures (Body Mass Index, waist circumference).

Other measures used during the randomized controlled trial include:

a) Sociodemographic characterization, gender, age, academic qualifications, and profession, which will be collected through questionnaires;b) Clinical data, to be collected through questionnaires and patient records analysis, blood pressure, blood biomarkers, pathological history, and cardiovascular risk assessed through the Systematic COronary Risk Evaluation (SCORE) (37).

